##### Written Patient Educational Materials

We developed a low-literacy patient educational booklet that covers the following topics: 1. What Is Osteoarthritis?, 2.) Physical Activity and Osteoarthritis, 3. Weight Management, 4. Skills for Managing Pain (Cognitive Behavioral Strategies). Patients are asked to review these materials during the intervention period. The booklet also includes worksheets for documenting goals and action plans related to physical activity and weight management, as well as worksheets for documenting practice of cognitive behavioral skills.

##### Exercise Video

Participants are given a copy of an exercise video called *Take Control with Exercise*, created by the Arthritis Foundation. Participants are also given therapy bands, since these are used in some of the exercises on the video.

##### Relaxation CD

Breathing relaxation and progressive muscle relaxation are two skills covered in this intervention. Participants are given CDs with audio instructions to facilitate practice of these skills. These were developed specifically for this study.

#### Provider intervention

The Provider Intervention involves delivery of patient-specific recommendations, delivered at the point of care. Specific recommendations include the following: 

· Refer to physical therapist for evaluation and / or therapeutic exercises

· Refer for evaluation for knee brace

· Refer to weight management program

· Refer to physical activity program

· Perform or refer for intra-articular injection

· Recommend or prescribe Topical NSAID or Capsaicin

· Add gastroprotective agent or remove from NSAID (patient has risk factors for GI bleeding)

· Discuss discontinuation of OTC NSAID with patient (patient has risk factors for GI bleeding)

· Discuss the possibility of trying a new / alternate pain medication with patient

· Referral to orthopedic for evaluation for joint replacement surgery (if no contraindications)

These recommendations were selected on the basis of treatment guidelines for managing hip and knee OA [12-14,34]. For most of these treatments, there are not specific criteria (e.g., level of pain severity) to guide use. Therefore our study team and other content experts developed algorithms that guide when a treatment option would be reasonable for a PCP to consider for a given patient. Algorithms are shown in Additional file 1. Data that feed into these algorithms are derived from medical records and baseline assessments (including both objective measures and patient self-report measures). The study team monitors upcoming visits for all participants enrolled in the Provider Intervention, and recommendations are delivered to PCPs within about one week prior to participants’ first routine (non-urgent) visit after enrolling in the study. These recommendations are delivered to PCPs within the electronic medical record systems. Within the VA system, the study team provides PCPs with specific instructions for requesting consults for some of the recommendations, including knee braces (specific types); physical therapy visits, referral to the MOVE! weight management program, and orthopedic service visits for joint injections and evaluation for surgery. For each Duke clinic, the study team provides a list of local resources for physical activity and weight management programs to which PCPs may refer or direct patients.

### Measures

#### Overview and timing

For both VA-based and Duke-based studies, the primary time point for outcome assessment is 12-months following baseline assessment. Baseline and 12-month assessments are conducted in-person (except when transportation or time constraints require completion of portions of the questionnaire via telephone). We are also measuring the primary outcome (and a few other selected outcomes) via telephone at 6-months following baseline to examine the time trajectory of changes during the study period. For the Duke-based study, we will additionally evaluate the primary and several other outcomes at 18-months and 24-months following baseline, via telephone, to examine the sustainability of any intervention effects observed at the 12-month observation point.

#### Primary and secondary outcomes

The primary outcome measure for this study is the WOMAC, a measure of lower extremity pain (5 items), stiffness (2 items), and function (17 items). Secondary outcomes are objective physical function and depressive symptoms, as these are both key outcomes for patients with OA and are associated with pain. Objective physical function is being assessed with the Short Physical Performance Test Protocol [35], which is a series of five tests covering the domains of balance (3 tests), gait speed (8-foot walk), and time to rise from a chair and return to the seated position five times. Depressive symptoms are being assessed with the Patient Health Questionnaire (PHQ-8), a reliable and valid measure of depression [36].

#### Process / intermediate measures

Several process measures are being evaluated in order to describe changes in intermediate outcomes that may be associated with the interventions, either as mediating or moderating factors. Process measures include the Arthritis Self Efficacy [37], Self-Efficacy for Exercise scale [38], Perceived Competence for Maintaining a Healthy Diet [39], physical activity (Community Health Activities Model Program for Seniors; CHAMPS) [40,41], dietary intake using the Block Brief 2000 Food Frequency Questionnaire (3-Month Recall) [42], Pain Catastrophizing Scale [43], Stone and Neale’s Daily Coping Inventory adapted for pain coping [44], and the number of completed intervention calls (for those in the patient intervention groups).

#### OA-related treatments and medical care

We are asking patients to report their use of OA-related treatments, including: visits to physical therapists, visits to orthopedic surgeons, receipt of joint injections, use of knee braces, pain medication use, and topical analgesic use. These data will allow us to evaluate whether there are any differences in OA treatments (during the study period) between patients of providers / clinics who are in the Provider intervention vs. Provider control arms.

#### Participant characteristics

We are collecting patient demographic and clinical characteristics including: self-reported age, gender, race/ethnicity, household financial situation, education level, marital status, work status, health literacy (using the Rapid Estimate of Adult Literacy -SF) [45], body mass index, history of knee and hip injuries and surgeries, duration of OA symptoms, general self-rated health, smoking, alcohol use, and comorbid illnesses using the Self-Administered Comorbidity Questionnaire [46].

#### Exploratory measures

In addition, we are collecting exploratory measures that are of interest in this patient population and type of intervention. These measures include additional pain measures (visual analog and visual numeric scales [47,48], measure of pain predictability from the Measure of Constant and Intermittent Osteoarthritis Pain [49]), fatigue visual analog scale [48], sleep quality (Insomnia Severity Index [28] and Berlin Questionnaire [50]), foot symptoms (Foot Assessment Clinical Tool [51]), Social Support for Diet and Exercise [52], Satisfaction with Physical Function [53], and Global Assessment of Joint Symptom Change (at follow-up only [54,55]). At follow-up we will also assess perceptions of patients and providers about the respective interventions, as well as suggestions for improvements for future implementation, using open-ended questions.

### Sample size

For the VA-based study, we will enroll approximately 30 providers (15 per group) with 10 patients per provider (150 per group), for a total sample size of 300. Our goal was to have sufficient sample size to detect a moderate effect size of approximately 0.30 for the primary hypothesis with 80% power and a type-I error rate (alpha) of 0.05. Based on expected mean baseline WOMAC scores of 38 with a standard deviation of 14 (anticipated from our prior pilot work), this effect size translates to a 4.2 point difference at 12-months, which is equivalent to approximately 11% improvement from baseline scores. Sample size calculations were based on methods appropriate for ANCOVA type analyses [56] and adjusted for provider clustering using the method of Donnar & Klar [57]. A correlation of 0.60 between time points was estimated based on our pilot data, and we accounted for a 12% attrition rate. This yielded a final sample size of 150 participants per group.

For the Duke-based study, we will enroll approximately 56 participants across each of 10 clinics, for a total sample size of 560. Our goal was to have sufficient sample size to detect moderate effect size of approximately 0.39 for the primary hypotheses with 80% power and a type-I error rate (alpha) of 0.05. Based on the same pilot data described above, this effect size translates to a 5.5 point difference at 12-months which is equivalent to approximately 15% improvement from baseline scores. For H_1_, this implies that compared to usual care we can detect a 15% greater improvement in WOMAC scores for participants that receive the combined intervention than the improvement in WOMAC scores for participants that receive either the Patient or Provider only at 12-months. For H_2_, this implies we can detect a 15% greater improvement in those that receive either the Patient or Provider intervention as compared to usual care at 12-months. Sample size calculations were based on methods appropriate for ANCOVA type methods, [56] adjusted for clinic clustering using the method of Donnar & Klar [57]. A correlation of 0.60 between time points was estimated based on our pilot data, and we accounted for a 15% attrition rate. This yielded a final sample size of 140 participants per group.

### Data analyses

The main conclusions drawn from these trials will be based on the pre-specified primary and secondary hypotheses and will be tested with two-sided p-values at the standard 0.05 level. Primary analyses will be conducted on an intent-to-treat basis; participants will be analyzed in the group to which they were assigned, regardless of intervention adherence, using all data up to the 12-months follow-up or last available measurement prior to exclusion or dropout [58]. Statistical analyses will be performed using SAS for Windows (Version 9.2: SAS Institute, Cary, NC) and R (http://www.R-project.org).

For the VA-based study, our primary hypothesis will be tested using a hierarchical linear model with patients nested within providers; baseline, 6- and 12-month values in the response vector will be used to estimate changes in WOMAC scores over time and test the primary hypothesis [59]. A random effect will be included in the model to account for clustering of patients within providers, as the providers are the unit of randomization. Because of the small number of time points, we will apply an unstructured covariance matrix to take into account the within-patient correlation between repeated measures over time. The predictors in the model will include a dummy coded time effect and an indicator variable for the intervention interacting with the time effect. The fixed-effect portion of the model will have the form [60]

(1)$$Y_{\mathrm{ijk}}=\beta_{0}+\beta_{1}*\left(time6\right)+\beta_{2}*\left(time12\right)+\beta_{3}*\left(intervention*time6\right)+\beta_{4}*\left(intervention*time12\right)$$

We will estimate the parameters in the model using the SAS procedure MIXED (Cary, NC). This method handles dropout in a principled manner. However, depending on the type and scope of any missing data, we will also explore multiple imputation as a strategy to use in conjunction with our primary analytic tools [61]. As recommended in the Committee for Proprietary Medicinal Products guidelines, the primary (as well as secondary) analyses will include the race stratification variable as a fixed covariate in the main analytic models. Secondary analyses will be conducted in a similar manner, testing for differences in physical function and depressive symptoms.

For the Duke-based study, our two primary hypotheses will also be tested using a similar hierarchical linear model, with patients nested within clinic. The predictors in this model will include a dummy coded time effect and separate indicator variables for the Provider and Patient interventions interacting with the time effect. The fixed-effect portion of the model will have the form

(2)$$\begin{array}{l} Y_{\mathrm{ijk}}=\beta_{0}+\beta_{1}*\left(time6\right)+\beta_{2}*\left(time12\right)+\beta_{3}*\left(provider*time6\right)+\beta_{4}*\left(patient*time6\right)\\ +\beta_{5}*\left(provider*patient*time6\right)+\beta_{6}*\left(provider*time12\right)+\beta_{7}*\left(patient*time12\right)\\ +\beta_{8}*\left(provider*patient*time12\right) \end{array}$$

for clinic *i*, patient *j*, at time *k*.

The specific test for H_1_ based on the above model parameterization is testing that *β*_*8*_ equals zero. For H_2_, for the Provider intervention alone compared to usual care at 12-months is a test of *β*_*6*_ equal 0 and for the Patient intervention only it is *β*_*7*_ equal zero*.* The primary (as well as secondary) analyses will include the race and gender stratification variable as a fixed covariate in the main analytic models. Secondary analyses will be conducted in a similar manner, testing for differences in physical function and depressive symptoms.

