### Hypotheses

Hypotheses for the VA-based study (reflecting a 2-arm trial) are:

Primary

H_1_: Patients with hip and/or knee OA who receive a comprehensive intervention (including both patient-based and provider-based components) will have a larger, clinically relevant improvement in self-reported pain, stiffness and function, as measured by the Western Ontario and McMasters Universities Osteoarthritis Index (WOMAC), compared with usual care.

Secondary

H_2_: The comprehensive OA intervention will result in improvement in objectively assessed physical function (using the Short Physical Performance Test Protocol) when compared to usual care.

H_3_: The comprehensive OA intervention will result in improvement in depressive symptoms (measured with the Patient Health Questionnaire-8 (PHQ-8) [24]) when compared to usual care.

Hypotheses for the Duke-based study (reflecting a 4-arm trial) are:

Primary

H_1_: Compared to usual care, patients with hip and/or knee OA who receive a combined patient-based and provider-based intervention will have a larger improvement in self-reported pain, stiffness and function, as measured by the WOMAC, than either a provider-based or patient-based intervention alone.

H_2_: Patients with hip and/or knee OA who receive either the patient-based OR provider-based intervention will have clinically relevant improvements in WOMAC scores when compared to usual care.

Secondary

H_3_: The patient-based, provider-based, and combined interventions will each result in improvement in objectively assessed physical function (using the Short Physical Performance Test Protocol) when compared to usual care, and the combined intervention will result in the greatest improvement.

H_4_: The patient-based, provider-based, and combined interventions will each result in improvement in depressive symptoms (measured with the PHQ-8 [24]) when compared to usual care, and the combined intervention will result in the greatest improvement.

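### The main conclusions may rest on any primary or secondary hypothesis, each tested at two-sided 0.05 with no order among them; restrict them to the primary hypotheses and label 0.05 as a per-test level

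*Protocol article*

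**What the plan says.** The rule is in the protocol article, Data analyses, first paragraph, which rests the main conclusions of both trials on the pre-specified "primary and secondary hypotheses and will be tested with two-sided p-values at the standard 0.05 level". Primary and secondary hypotheses appear side by side, and neither is made conditional on the other.

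For the Duke trial the same section says that "our two primary hypotheses will also be tested using a similar hierarchical linear model, with patients nested within clinic". It then names three tests at 12 months: β8 (provider × patient) for H1, and β6 (Provider alone) and β7 (Patient alone), each against usual care, for H2. The Hypotheses section words H2 as patients "who receive either the patient-based OR provider-based intervention will have clinically relevant improvements in WOMAC scores when compared to usual care". H3 and H4 say that each of the three interventions improves on usual care, on physical performance and on depressive symptoms.

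The Sample size section plans Duke to detect its effect "for the primary hypotheses with 80% power and a type-I error rate (alpha) of 0.05".

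The VA trial has one primary hypothesis, with one test, and two secondary hypotheses. The article gives no ordering, gate, split of alpha or adjustment for either trial.

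**The concern.** A level of 0.05 describes one test. The article attaches the main conclusions to a set of tests: three primary ones in Duke plus at least six secondary ones, and one primary plus two secondary in VA. Without an order, nothing in the text stops a single significant depression or physical-performance contrast from being presented as a main conclusion when the WOMAC result is null. A reader who takes the planning alpha of 0.05 to describe the Duke primary hypotheses together would also underestimate how often one of the three is significant by chance.

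**Working it through.** **Inputs from the article.** Two-sided 0.05 per test (Data analyses). Duke: four arms of 140 and primary tests β6, β7 and β8 (Sample size; Data analyses). Secondary outcomes: physical performance and PHQ-8 (Hypotheses). VA: two arms and three outcomes. The clinic intraclass correlation (ICC) and the correlation between outcomes are not given, so both are varied below as assumptions.

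**The stated level.** Taken one at a time, each test has a 5% two-sided error rate, as the article says, and 2.5% in the beneficial direction.

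**Duke primary family, no clustering.** Let U, T, P and C be the mean outcomes under usual care, Patient, Provider and Combined, each with variance v.
- β6 = P − U and β7 = T − U. Each has variance 2v and their covariance is v, so the correlation is 1/2 = 0.5.
- β8 = C − T − P + U has variance 4v. Its covariance with β6 or β7 is −2v, so the correlation is −2/√(2 × 4) = −0.707.

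Simulating this joint normal distribution with no true effects, each test at |z| > 1.96:

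| Duke primary tests | Significant in either direction | Significant in the beneficial direction |
|---|---|---|
| One test | 5% | 2.5% |
| β6 or β7 (H2) | 9.1% | 4.5% |
| β6, β7 or β8 (H1 and H2) | 11.3-11.4% | 7.1% |

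Bounds for comparison: 1 − 0.95² = 9.75% and 1 − 0.95³ = 14.3% if the tests were independent; 3 × 0.05 = 15% by Bonferroni.

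**With clinic clustering.** Clinics are nested in the provider arm. For an assumed ICC of 0.01 to 0.10, the H2 pair moves to 9.2-9.6% and all three tests to 11.7-12.5%, in either direction.

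**Adding the Duke secondaries.** Three arm-versus-usual-care contrasts on each of two outcomes make 3 + 6 = 9 tests. With shared arms and an assumed correlation between outcomes of 0 to 0.7, the chance of at least one significant result in either direction runs from 32% down to 26%. Independence would give 1 − 0.95⁹ = 37%. That figure is a reference only, because all nine tests share patients and the usual-care arm.

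**VA.** Three outcomes with one contrast each: 1 − 0.95³ = 14.3% at zero correlation, falling to 11% at 0.7.

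**Cost of adjusting the Duke primaries.** A test with exactly 80% power at 0.05 has a standardized effect of 1.960 + 0.842 = 2.802. At Holm's first step the level is 0.05/3 = 0.0167, with critical value 2.394. Power becomes Φ(2.802 − 2.394) = 66%. Restoring 80% multiplies the sample size by (2.394 + 0.842)²/(1.960 + 0.842)² = 1.33, so 140 per group becomes about 187. The 80% start is nominal: without the ICC, 140 per group can be matched but not confirmed.

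**The case against.** - **The level is per test.** Testing at 0.05, and an alpha in a sample-size calculation, read naturally as per-test levels. This stands. A reader might infer that the stated type I error of 0.05 is really 9-11% and therefore misstated. The article does not support that, because it never calls 0.05 familywise.
- **Direction.** H1 and H2 predict improvement, while 9% and 11% count harm and antagonism too. This stands: the beneficial-direction figures are 4.5% and 7%, against 2.5% for one test. There is inflation, but a claim that a null Duke trial yields a false benefit on its primary tests far more often than 5% of the time would be too strong.
- **Distinct questions.** Provider alone, Patient alone and their interaction are separately named hypotheses, and testing each at its own 0.05 is widely defended in factorial-type trials. This stands in part, and is why adjustment among the Duke primaries is left optional. A reader might also take the wording of H2 as an any-win rule. That is only one reading, since the analysis section gives each intervention its own test. The argument does not reach main conclusions drawn from secondary outcomes.
- **The sentence on main conclusions may only exclude tests that were not pre-specified.** That is possible. The article does not say that a secondary result may replace a failed primary one; it only leaves that open by putting both on the same footing.
- **Multiplicity belongs in the analysis plan.** Silence could be left to it. Here the protocol states a rule, and a hierarchy in an analysis plan would have to override it.

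**Conclusion.** The concern holds in limited form. The rule fixed in Data analyses lets primary and secondary tests, each at two-sided 0.05, support the main conclusions without any order. For Duke the chance of at least one significant primary test under no effect is about 11% in either direction, slightly more with clustering, and about 7% in the beneficial direction. With six secondary contrasts it is about 26-32% in either direction. VA has no multiplicity among primaries; the 11-14% arises only if its secondaries share the main conclusions.

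These figures assume no true effect of any intervention on any outcome, equal arms and normal test statistics. The ranges also rest on assumed correlations between outcomes, and the clustered values on assumed ICCs. This is a wording improvement worth making, not an error in a reported number. Whether β8 is the right test of H1 is a separate issue and is not judged here.

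**What to change.** 1. In Data analyses, change the sentence on main conclusions: in each trial they rest on the primary WOMAC hypotheses. A secondary hypothesis is confirmatory only if the related primary test succeeds, and is otherwise supportive. Name the related primary test for every secondary contrast. The Duke Combined-versus-usual-care contrasts need this most, as none of β6, β7 and β8 is that contrast.
2. In Sample size and Data analyses, state that 0.05 is the level of each test, and that the chance of at least one significant Duke primary test under no effect is about 11%, slightly higher with clinic clustering.

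Under no effect, item 1 brings the chance of any confirmatory claim back to that of the primary tests (about 11% in Duke, 5% in VA), because no secondary can count unless a primary test was already significant. It costs the primary tests no power and changes no data collection. The price is that a significant secondary result after a failed primary can no longer carry a main conclusion.

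Holm across the three Duke primary tests is optional. It would hold that family at 0.05, but at its first step it lowers a nominal 80% power to about 66%, or requires about 187 instead of 140 per group.

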## Methods / Design

### Trial design

Both the VA-based and Duke-based studies are randomized controlled trials, but the study designs differ due to variations in the arms being tested. The VA-based study is a cluster randomized controlled trial, in which Primary Care Providers (PCPs) are assigned to one of two study arms: OA Intervention and Usual Care Control. PCPs assigned to the OA Intervention receive the Provider Intervention described below, and their enrolled patients receive the Patient Intervention, also described below.

Figure 1 shows the design of the Duke-based trial, in which clinics are randomized to Provider Intervention vs. Control, then patients within those clinics are assigned to Patient Intervention vs. Control. This results in patients being assigned to one of four study arms: 1.) Patient Intervention Only, 2.) Provider Intervention Only, 3.) Patient Intervention + Provider Intervention and, 4.) Usual Care Control. For both VA and Duke studies, all participants continue with any other usual medical care they receive for OA. After completion of follow-up assessments, participants assigned to the Patient Control condition are given the materials for the Patient Intervention, and clinics / PCPs who were assigned to the Provider Control condition are given the patient-specific recommendations for the Provider Intervention. These studies were reviewed and approved by the Durham VA Medical Center and Duke Institutional Review Boards, respectively.

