### Randomization

Randomization for both studies is based on a computer generated sequence maintained by the project statistician. For the VA-based study, we stratify randomization of providers according to high vs. low volume of female patients (<15% vs. ≥15%), to ensure the groups are balanced in this respect. For the Duke-based study, clinics are randomized in pairs that are selected based on common characteristics such as approximate patient panel size and PC specialty (Family Medicine vs. Internal Medicine). For both studies, patient randomization is stratified according to race (white / non-white), and the Duke-based study is also stratified by patient gender. This is important because there are known differences in OA-related pain and function according to both gender and race, and it is possible that intervention effects may differ across these demographic variables as well.

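### The VA analysis adjusts for race as if it had stratified allocation, but names no term for the factor that did stratify it: providers' volume of female patients

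*Protocol article*

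**What the plan says.** All references are to the protocol article.

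- **Trial design.** "The VA-based study is a cluster randomized controlled trial, in which Primary Care Providers (PCPs) are assigned to one of two study arms". For providers in the intervention arm, "their enrolled patients receive the Patient Intervention, also described below". No separate allocation of VA patients is described.
- **Data analyses (VA).** The provider random effect is justified "as the providers are the unit of randomization".
- **Randomization (VA, provider level).** "we stratify randomization of providers according to high vs. low volume of female patients", with the cut at 15%, so that the arms are balanced on it.
- **Randomization (both trials, patient level).** "For both studies, patient randomization is stratified according to race (white / non-white"); Duke is also stratified by patient gender.
- **Participants.** Race enters the VA trial as a recruitment target of 5 white and 5 non-white patients per provider.
- **Data analyses (VA covariates).** With reference to a regulatory guideline, "the primary (as well as secondary) analyses will include the race stratification variable as a fixed covariate in the main analytic models". Equation (1) has time and intervention-by-time terms only. Neither the equation nor the text names the female-volume stratum.
- **Duke.** "clinics are randomized in pairs that are selected based on common characteristics such as approximate patient panel size and PC specialty". The Duke model names race and gender as covariates and has a clinic level, but no term for pair, panel size or specialty.

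**The concern.** There are two linked faults in what the article states about the VA trial.

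The first is a contradiction. Trial design and Data analyses make the provider the randomised unit. Randomization speaks of a race-stratified patient randomisation in both trials. In VA there is nothing at patient level to stratify.

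The second follows from it. Data analyses puts a variable in the model because it is the stratification variable, and in VA that is the wrong variable. The factor used to balance the provider arms is left unnamed. When allocation is forced to balance on a prognostic factor but the model ignores it, the factor's variation stays in the between-provider error. The model's standard error is then larger than the true sampling variability of the estimate, so the test rejects a true null less often than 5% and some power is lost. Randomization itself says that OA pain and function differ by gender, so on the authors' own reasoning the stratum could be prognostic.

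**Working it through.** **1. What was randomised, and on what**

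| | VA | Duke |
|---|---|---|
| Randomised unit | Provider only | Clinic, then patient within clinic |
| Cluster-level factor | Female-patient volume | Clinic pair (panel size, specialty) |
| Patient-level factor | None possible | Race, gender |
| Covariates named in the model | Race | Race, gender |

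In Duke the named covariates are the patient-level strata. In VA the named covariate is no stratum at all, and the one real stratum is absent.

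**2. The ICC implied by the VA sample size**

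The article gives no ICC, so it is backed out from the Sample size section: effect 0.30 SD, 80% power, two-sided 0.05, correlation 0.60, attrition 12%, 10 patients per provider, 150 per arm.

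- Unadjusted n per arm: 2 × ((1.960 + 0.842)/0.30)² = 174.4, rounded up to 175.
- ANCOVA: 174.4 × (1 − 0.60²) = 111.6.
- Stated size net of attrition: 150 × 0.88 = 132.
- Implied design effect: 132/111.6 = 1.18.
- Implied ICC: 0.18/(10 − 1) = 0.02. Worked forward, ICC 0.02 with 10 patients per provider returns exactly 150 per arm.

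**3. Effect of leaving out the stratum under model (1)**

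Model (1) has no intervention main effect, so the arms share a common baseline mean and the 12-month effect (β4) is baseline-adjusted. Set total variance to 1, with 10 patients per provider and 15 providers per arm, ignoring attrition. For provider means:

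- V = provider variance + 0.98/10 (variance at one time)
- C = provider covariance + residual covariance/10 (baseline with 12 months)
- Var(β4) = (2/15) × (V − C²/V)

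Let the stratum explain 25%, 50% or 75% of the provider variance of 0.02. This share is an assumption; the article gives no figure. Adjustment removes that share.

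*Provider effect constant over time* (provider covariance equals provider variance; residual covariance 0.60 − 0.02 = 0.58):

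| Share removed | V | C | V − C²/V | Excess SE if omitted |
|---|---|---|---|---|
| 0 (omitted) | 0.118 | 0.078 | 0.06644 | – |
| 25% | 0.113 | 0.073 | 0.06584 | √(0.06644/0.06584) − 1 = 0.5% |
| 50% | 0.108 | 0.068 | 0.06519 | 1.0% |
| 75% | 0.103 | 0.063 | 0.06447 | 1.5% |

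*Provider effect correlated 0.6 over time* (residual covariance 0.60 − 0.012 = 0.588). Here C/V = 0.6 throughout, so the V − C²/V term is 0.64 × V:

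- 25%: √(0.118/0.113) − 1 = 2.2%
- 50%: √(0.118/0.108) − 1 = 4.5%
- 75%: √(0.118/0.103) − 1 = 7.0%

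The first case is smaller because a constant provider effect largely cancels against baseline.

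**4. What that does to the test**

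An SE inflated by a factor f gives a null rejection rate of about 2 × Φ(−1.96 × f). At f = 1.015 this is 4.7%; at f = 1.07 it is 3.6%. Rejection stays below 5% in every case.

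**5. Duke**

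Patients are randomised within clinics, so the clinic effect cancels from the patient contrast (β7) and from the interaction (β8). Applying the same generalised least squares calculation to model (2), with 10 clinics and 28 patients per patient arm per clinic, leaves the standard errors of β7 and β8 unchanged. Only β6 moves: by 0.4-2.1% with a time-constant clinic effect, ICC 0.015-0.03 and the same 25-75% share, and by more if clinic effects drift. Clinic-level degrees of freedom are 10 − 2 = 8, or 5 − 1 = 4 with pair effects, which raises the critical t from 2.31 to 2.78.

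**The case against.** The strongest reply is that this is a wording slip in an article describing two trials at once. Data analyses states plainly that VA providers are the randomised unit, so few readers would be misled. The text says race will be included, not that nothing else will be. The equations omit even race and gender, so they are not full covariate lists. An unseen analysis plan may add the stratum. Adjusting for race is harmless, since race is a genuine VA design variable through the quota.

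Much of this stands. Race should stay in the model, and the equations alone prove no omission. A reader might also infer that the plan breaches the guideline it cites. The article does not show this: it names one variable and states no general rule, and the guideline is not at hand.

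The reply does not dispose of the point. This is not a detail merely left out: the text names the stratification covariate for the main VA models and names one that did not stratify VA allocation.

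The objection on size also stands in large part. A stratum share of 25-75% is not supported by anything in the article. With two equal strata, ICC 0.02 and SD 14, the between-provider SD is 14 × √0.02 = 1.98 points. The strata would then have to differ in mean WOMAC by 2 × 1.98 × √0.25 = 2.0 to 2 × 1.98 × √0.75 = 3.4 points.

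**Conclusion.** The point holds as a correction to the VA text and model. The Randomization section is wrong for VA, race is mislabelled there, and the real stratum has no named term.

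The effect is minor: an excess standard error of about 0.5-1.5% with time-constant provider effects, or 2-7% if provider effects vary over time with correlation about 0.6. Both ranges rest on the implied ICC of 0.02 and the assumed 25-75% share. A weaker stratum means a smaller loss.

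Three stronger readings are not supported:

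- **That VA patients are randomised within provider.** Trial design and Data analyses both rule this out.
- **That the omission biases the effect or inflates type I error.** It makes the test slightly conservative.
- **That the Duke model is wrong because it leaves out the clinic pairing.** β8 (the test of H1) and β7 (the patient part of H2) are unaffected. For β6, adjustment trades precision against scarce clinic-level degrees of freedom, so leaving the pairing out of the main model is defensible.

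**What to change.** 1. **Randomization section.** State that race-stratified patient randomisation applies to Duke only. For VA, say that providers are randomised within strata of female-patient volume and that race is a recruitment quota within provider.
2. **Data analyses, VA.** Keep race as a fixed covariate, but describe it as a quota and prognostic covariate.
3. **VA primary and secondary models.** Add the female-volume stratum (<15% vs ≥15%) as a fixed effect. Include its time interactions if it is to affect the 12-month contrast when provider effects vary over time.
4. **Duke, optional.** Give an analysis of the provider contrast adjusted for specialty and panel size, or for pair, as a sensitivity analysis.

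The cost is wording plus about 1 of 28 provider-level degrees of freedom in VA, where the critical t goes from 2.048 to 2.052. The stratum was needed to randomise, so no new data are required. The covariate set should be fixed before outcomes are analysed by arm.
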